## Abstract

Patients surviving head and neck cancer (HNC) suffer from high physical, psychological, and socioeconomic burdens. Achieving cancer-free survival with an optimal quality of life (QoL) is the primary goal for HNC patient management. So, maintaining lifelong surveillance is critical. An ambitious goal would be to carry this out through the advanced analysis of environmental, emotional, and behavioral data unobtrusively collected from mobile devices. The aim of this clinical trial is to reduce, with non-invasive tools (i.e., patients’ mobile devices), the proportion of HNC survivors (i.e., having completed their curative treatment from 3 months to 10 years) experiencing a clinically relevant reduction in QoL during follow-up. The Big Data for Quality of Life (BD4QoL) study is an international, multicenter, randomized (2:1), open-label trial. The primary endpoint is a clinically relevant global health-related EORTC QLQ-C30 QoL deterioration (decrease ≥10 points) at any point during 24 months post-treatment follow-up. The target sample size is 420 patients. Patients will be randomized to be followed up using the BD4QoL platform or per standard clinical practice. The BD4QoL platform includes a set of services to allow patients monitoring and empowerment through two main tools: a mobile application installed on participants’ smartphones, that includes a chatbot for e-coaching, and the Point of Care dashboard, to let the investigators manage patients data. In both arms, participants will be asked to complete QoL questionnaires at study entry and once every 6 months, and will undergo post-treatment follow up as per clinical practice. Patients randomized to the intervention arm (n=280) will receive access to the BD4QoL platform, those in the control arm (n=140) will not. Eligibility criteria include completing curative treatments for non-metastatic HNC and the use of an Android-based smartphone. Patients undergoing active treatments or with synchronous cancers are excluded.

Clinical Trial Registration: ClinicalTrials.gov, identifier (NCT05315570).

## Introduction

1

Depending on disease stage, head and neck cancer (HNC) can be cured either with single modality or with multimodal treatments, consisting of various combinations of surgery, radiotherapy and chemotherapy. Despite treatment with curative intent, loco-regional recurrences and/or distant relapses are frequent. Moreover, these therapeutic approaches result in significant acute toxicities and late sequelae. Therefore, quality of life (QoL) is often impaired in these survivors. It is known that QoL is a prognostic factor because it is related to overall survival in cancer patients (1) and to loco-regional control in HNC patients (2). Published studies suggest that even though people having undergone treatment for HNC usually recover their global QoL by 12 months after treatment, persistent late sequelae are observed, notably poor physical functioning, fatigue, xerostomia and sticky saliva (3).

Three main validated QoL questionnaires will be used: EORTC QLQ-C30 for all types of malignancies (4), EORTC HN43 [an updated version of the formerly used H&N35 questionnaire (5)] for HNC patients only (6), EQ-5D-5L (7) which is a patient-reported measurement focused on five domains (mobility, self-care, usual activities, pain/discomfort, and anxiety/depression), that can be used for assessment of health status and also for health technology assessment (HTA) (8). Interestingly, in some subsets like nasopharyngeal carcinoma, differences in QoL are independent predictors of prognosis (9). In the context of patient-reported outcome measurements (PROMs), the cancer behavior inventory (CBI) (10) and its brief version (CBI-B) (11) are validated instruments aimed at measuring self-efficacy strategies for coping with cancer. Specifically, self-efficacy for coping with cancer is a psychosocial construct referring to people’s beliefs about their capabilities of effectively executing behaviors that occur in the course of dealing with a cancer diagnosis, cancer treatments, and transitioning to survivorship (12). The results of a recent meta-analysis attest that cancer patients with higher coping self-efficacy report a higher quality of life (12). In the clinical and research contexts, the CBI-B represents a useful adjunct to other PROMs because it allows detection of cognitive changes in personal, control, and psychosocial adjustment and identification of patients who need further psychosocial services (11).

In order to minimize the risk of data misinterpretation and to maximize the precision and the accuracy in measuring QoL variations effectively, clinically meaningful differences in QoL scales have been suggested. In particular, when considering an overall indicator such as global health status according to EORTC QLQ-C30 a deterioration is considered clinically relevant if there is a reduction in at least 10 points of the score (13, 14).

Predictive factors for identifying which HNC patients are at higher risk of suffering long-term poor QoL have not yet been identified. To date, the only way we can work out if someone has poor long-term QoL is to administer repeated QoL questionnaires during follow-up. Avoiding QoL deterioration, even if temporary, is a critical clinical need. An ambitious goal would be to detect early variations in QoL (or in other measures potentially predicting later QoL deterioration) that translate into a tangible benefit (e.g., early diagnosis of incoming and evolving health status) that improves long-term QoL in HNC survivors. The combination of big-data analysis techniques and innovative use of information technology (IT) tools (e.g., smartphones) may allow targeted interventions to improve QoL. The results of a pilot study conducted on patients treated with palliative intent for gynecological cancers illustrated the potential benefits of such an approach (15). A mobile health intervention collecting both PROMs and activity data as a measure of health status was shown to be feasible and acceptable. Moreover, this was perceived to be effective in improving symptom management in patients with advanced gynecologic cancers. Most of the evidence on eHealth solutions in HNC patients is made of pilot or feasibility studies. The results of a non-blinded randomized controlled trial evaluating Oncokompas, an eHealth application aimed at supporting self-management of symptoms and health-related quality of life in cancer survivors, including HNC, were published in 2020 (16). Oncokompas did not improve knowledge, skills, and confidence in self-management in cancer survivors. However, the median follow-up of patients included in this study was only 6 months (after treatment conclusion), thus possibly preventing the observation of late QoL declines in most subjects. The study included 185 HNC patients (99 in the intervention arm, 86 in control one) enrolled across 14 Dutch hospitals in 19 months. This means an average of 9 patients recruited per year per center. Only 68 out of the 99 (68%) HNC patients in the intervention arm, and only 64 out of the 86 patients (74%) in the control arm returned a second questionnaire after 6 months. Therefore, only 132 of the 185 HNC patients (71%) remained in the study. This means that a 30% drop-out was observed over a six-month period.

The main aim of the present study is to anticipate and reduce, with the use of the non-invasive Big Data for Quality of Life (BD4QoL) platform (described below), the proportion of HNC survivors experiencing a clinically relevant reduction in QoL. If the participants report or are identified as having a significant finding during monitoring, a specific set of interventions will be applied if symptoms and findings on monitoring indicate their application. This clinical trial was designed and set up in the framework of the BD4QoL research project (full project title “Big Data Models and Intelligent tools for Quality of Life monitoring and participatory empowerment of head and neck cancer survivors”), that lasts 5 years and is funded by the European Commission (further details are specified in Section 7) (17). The BD4QoL Consortium is an interdisciplinary partnership made of several partners from seven European Countries, combining the complementary competences, skills, structural and infrastructural capabilities.

The adoption of mobile technologies of everyday use (i.e., embedded into standard mobile phones) for behavior reconstruction and linkage of behavior modifications to quality of life indicators, and the realization of predictive models for quality of life modifications will allow seamless and unobtrusive data capture over time, making the execution of clinical investigations more precise and less burdensome as compared to standard (manual) data capture. Artificial intelligence (AI) algorithms, including Machine Learning, Transfer Learning, Deep Learning-Based Models, Knowledge-Based Activity Models (Expert Activity Models – EAM) for behavior patterns recognition, IBM Watson technologies for affective computing such as Tone Analyzer, Natural Language Classifier, Natural Language Understanding, will be used.

## Methods and analysis

2

### Study objectives and endpoints

2.1

The overall aim of this study is to assess if QoL deterioration can be anticipated and prevented by the addition of the BD4QoL platform to standard of care (SoC) versus SoC alone, in HNC survivors post-treatment with up to 24-month follow-up. Primary and secondary objectives and endpoints are specified in **Table 1**, exploratory ones in **Table 2**.

**Table 1 T1:** Study objectives and endpoints.

	Objective	Endpoint
** *Primary* **	To reduce the proportion of HNC subjects experiencing a clinically meaningful deterioration of QoL between at least 2 visits during post-treatment follow-up.	The proportion of HNC survivors experiencing a clinically relevant deterioration in the global health scale of the EORTC QLQ-C30 [decrease ≥10 points, as defined in (13,14)] within the study observation (up to 24 months) period during post-treatment follow-up.
** *Secondary* **	To delay the time to the first clinically meaningful deterioration of QoL between at least 2 visits during post-treatment follow-up.	The time to first clinically relevant deterioration of EORTC QLQ-C30 global score [decrease ≥10 points, as defined in(13,14)] measured within the study observation (up to 24 months) period during post-treatment follow-up.
	To reduce the proportion of HNC subjects experiencing a clinically relevant deterioration in pre-specified QoL domains between at least 2 visits during post-treatment follow-up.	The proportion of HNC survivors experiencing a clinically meaningful deterioration [as defined in (13,14)] of pre-specified EORTC QLQ-C30 scales (emotional functioning, role functioning, sleep) within the study observation (up to 24 months) period during post-treatment follow-up.
	To reduce the proportion of HNC subjects experiencing a clinically meaningful deterioration in pre-specified head and neck cancer specific QoL domains between at least 2 visits during post-treatment follow-up.	The proportion of HNC survivors experiencing a clinically relevant deterioration of pre-specified EORTC QLQ-HN43 scales (swallowing, problems with teeth, problems opening mouth, speech, social eating, fear of progression, emotional functioning, fatigue) within the study observation (up to 24 months) period during post-treatment follow-up.
	To reduce the proportion of HNC subjects experiencing a clinically meaningful deterioration in health status between at least 2 visits during post-treatment follow-up.	The proportion of HNC survivors experiencing a clinically meaningful deterioration [as defined in (7)] of EQ-5D-5L domains (mobility, self-care, usual activities, pain/discomfort, anxiety/depression) within the study observation (up to 24 months) period during post-treatment follow-up

**Table 2 T2:** Exploratory objectives and endpoints.

Exploratory objective	Exploratory endpoint
To assess the association of clinically relevant variations in QoL [EORTC QLQ-C30 and HN43 global scores (13, 14)] with disease recurrence and survival in HNC survivors within the study observation (up to 24 months) period during post-treatment follow-up.	Association of disease-free survival (DFS), event-free survival (EFS) and overall survival (OS) with clinically relevant variations (either increase or decrease, as appropriate according to scales) of EORTC QLQ-C30 and HN43 questionnaires, as defined in (13, 14).
To To analyze time-dependent variations of QoL (EORTC QLQ-C30 and HN43 scores) within the study observation (up to 24 months) period during post-treatment follow-up in HNC survivors assessing their association with recurrence and survival.	Association of disease-free survival (DFS), event-free survival (EFS) and overall survival (OS) with time-dependent clinically relevant variations (either increase or decrease, as appropriate according to scales) of EORTC QLQ-C30 and HN43 questionnaires, as defined in (13, 14).
To To analyze QoL scores (EORTC QLQ-C30 and HN43 scores) within the study observation (up to 24 months) period during post-treatment follow-up in nasopharyngeal cancer patients assessing their association with recurrence and survival.	Association of disease-free survival (DFS), event-free survival (EFS) and overall survival (OS) with clinically relevant variations (either increase or decrease, as appropriate according to scales) of EORTC QLQ-C30 and HN43 questionnaires, as defined in (13, 14), in nasopharyngeal carcinoma patients.
To reduce the proportion of HNC subjects experiencing a clinically meaningful deterioration in pre-specified EORTC QLQ-HN43 scales (not included in secondary endpoints) between at least 2 visits during post-treatment follow-up.	The proportion of HNC survivors experiencing a clinically meaningful deterioration [as defined in (13, 14)] of pre-specified EORTC QLQ-HN43 scales (pain in the mouth, problems with senses, body image, dry mouth and sticky saliva, coughing, social contact, neurological problems, sexuality, problems with shoulder, skin problems) within the study observation (up to 24 months) period during post-treatment follow-up.
For HNC survivors randomized in the BD4QoL platform group, using artificial intelligence techniques to build models to predict a QoL deterioration [EORTC QLQ-C30 and HN43 scores, EQ-5D-5L as defined in (7, 13, 14)] between at least 2 visits during within the study observation (up to 24 months) period during post-treatment follow-up.	The association of all the health-related data recorded by the BD4QoL platform **Supplementary Material** registered continuously within the study observation (up to 24 months) period during post-treatment follow-up with clinically relevant variations (either increase or decrease, as appropriate according to scales) of EORTC QLQ-C30 and HN43 questionnaires, as defined in (7, 13, 14)
To assess the association of clinically relevant variations of QoL [EORTC QLQ-C30 and HN43 global scores (13, 14)] with self-efficacy for coping with cancer in HNC survivors within the study observation (up to 24 months) period during post-treatment follow-up.	Association of clinically relevant variations (either increase or decrease, as appropriate according to scales) of EORTC QLQ-C30 and HN43 questionnaires, as defined in (13, 14), and self-efficacy for coping with cancer, defined as mean of the item scores at the CBI-B (11).
To reduce the proportion of HNC subjects experiencing a clinically meaningful deterioration of QoL between at least 2 visits during post-treatment follow-up, stratifying according to patients completing treatment within 12 months versus after 12 months.	The proportion of HNC survivors experiencing a clinically meaningful global health-related EORTC QLQ-C30 QoL deterioration [decrease ≥10 points, as defined in (13, 14)] within the study observation (up to 24 months) period during post-treatment follow-up. Stratification according to timing after study completion (less than 12 months versus more than 12 months)
To assess the economic impact on HNC survivor care and the viability, usability, and trust of using the BD4QoL platform (Health Technology Assessment, HTA).	Incremental Cost-Effectiveness Ratio measured in €/QALY. Measures of viability, usability, and trust.

### Study design

2.2

This is a multicenter, international, two-arm, randomized (2:1 ratio), open-label, superiority trial, designed to evaluate the proportion of HNC survivors experiencing a clinically meaningful QoL deterioration [reduction of at least 10 points in EORTC QLQ-C30 global health status (13, 14)] between at least 2 visits during post-treatment follow-up (up to 24 months from randomization) with the use of the BD4QoL platform through the web-forms tool for QoL questionnaires answers and through continuous monitoring by a mobile application (App) installed on the study subject’s mobile phone in comparison to those without the BD4QoL platform (SoC). If a clinically relevant deterioration in global health, measured with the EORTC QLQ-C30 global health scale [decrease ≥10 points, as defined in (13, 14)] is detected during the study period, the subject participation in the study will be interrupted (because the aforementioned decrease would imply that the primary endpoint is not met for a specific participant).

Patients will be followed up as per clinical practice (18, 19):

a. All subjects will be asked to complete validated questionnaires [EORTC QLQ-C30 (4), QLQ-HN43 (6), and EQ-5D-5L (7), CBI-B (11)] and PREM on up to 5 occasions over a 2-year period, at randomization (0-month of follow-up), then once every 6 months ± 2 months (after 6, 12, 18, 24 months from randomization).

b. Participants in both arms will be offered routine SoC and asked to complete validated QoL questionnaires at regular intervals (described above). In addition, those in the intervention arm will be offered the device-generated data collection platform (BD4QoL device *plus* QoL validated questionnaires *plus* counseling and physician contact triggered by the data generated by the platform [early intervention] *plus* a possible psychological effect of the whole activities in the interventional arm). A 2:1 randomization will be used (2/3 of subjects with BD4QoL platform versus 1/3 of subjects without). Participants randomized to the control arm will not receive the above-mentioned platform; they will fill in the same validated questionnaires on web-based instruments and will be followed up as per usual clinical practice.

The study design is summarized in **Figure 1**. The choice of unequal randomization in randomized controlled trials is rarely resorted to. The main reasons for its justification have been reviewed by Dibao-Dina et al. (20): obtaining more safety data, exposing fewer patients to the potentially inferior group, increasing patients acceptability, reducing costs.

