#### Sample size

2.5.1

The primary endpoint is the proportion of HNC survivors experiencing a clinically relevant deterioration in global health-related QoL as previously defined.

In the European BD2Decide project (31), funded by the Horizon 2020 program and concluded in November 2019, the analysis of QoL questionnaires was performed on over 450 stage III-IV HNSCC patients (recruited from Italy, Germany, and the Netherlands; data cut-off date 23^rd^ September 2019): at least two consecutive EORTC QLQ-C30 questionnaires filled in after at least 6 months of follow-up were available for 117 patients; among them, a clinically meaningful deterioration of QoL (reduction of at least 10 points) was observed in 22 (19%) cases during post-curative treatment follow-up.

The second historical cohort comprised 65 patients from Mainz (Germany) having EORTC QLQ-C30 questionnaires completed 24 and 36 months after curative surgery (32). In this population, the percentage of subjects experiencing a deterioration ≥ 10 points in EORTC QLQ-C30 global health status from the 24^th^ to the 36^th^ months after treatments was 23%.

In the Head and Neck 5000 project (UK) (33) repeated global health scores at 12 and 36 months after treatment were available for 1241 people with HNC. A clinically meaningful deterioration of QoL (reduction of at least 10 points) was observed in 18% of these subjects.

In these three existing studies, the average percentage (arithmetic mean) of HNC patients experiencing a clinically meaningful deterioration of EORTC QLQ-C30 global score (reduction of at least 10 points) during follow-up was 20% (19% BD2Decide, 23% Mainz, 18% HN5000). These findings are preliminary and will be explored further as part of the European Union (EU) program supporting this study.

The primary endpoint of this study is the proportion of patients showing a reduction of at least 10 points in EORTC QLQ-C30 global health status score in HNC survivors. Therefore, considering the null hypothesis (*H_0_
*) of no difference for the primary endpoint, the proportion of HNC survivors showing a reduction of at least 10 points in EORTC QLQ-C30 global health status during 24-month FU in the control group is 20% (*µ_0_
*), as derived from the historical benchmark data.

Considering the alternative hypothesis (*H_1_
*), the desired proportion of HNC survivors showing a reduction of at least 10 points in EORTC QLQ-C30 global health status during FU in the intervention group is 10% (*µ_1_

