#### Quality of life data and follow up information

2.6.3

Quality of life information related to enrolled participants will be collected through validated questionnaires: EORTC QLQ-C30 and EORTC QLQ-HN43. Health status will be measured using the EQ-5D-5L, coping behavior using the CBI-B, and one PREM. Specifically, the PREM will be a study-specific question, asking patients “Are you satisfied about the care you have received during the follow-up?” (the possible answers will be “Absolutely disagree (I am not satisfied at all)”, “Moderately disagree”, “Neither agree nor disagree”, “Moderately agree”, “Absolutely agree (I am very satisfied)”). Questionnaires will be collected at study entry and after 6-, 12-, 18-, 24-month from randomization.

Patients’ follow-up information will be collected after treatment termination and will be updated at each evaluation. Data related to the disease outcome (overall survival, OS; disease-free survival, DFS) will be collected up to 24 months from randomization (**Table 4**).

**Table 4 T4:** Study flowchart.

Procedure/evaluation	Randomization	Continuous (up to 24 months from study entry)	Months +6, +12, +18, +24 ( ± 2 weeks)
Informed consent	✓		
Baseline evaluation	✓		
Randomization	✓		
Demographics	✓		
Concomitant medications and medical events review	✓		✓
Clinical data retrieval (stage, pathology, HPV status)	✓		
Physical/emotional/social monitoring apps	✓	✓*	✓
QoL questionnaires	✓		✓

*for intervention arm only.

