#### Study interruption and withdrawal

2.6.7

Participation in the study will be interrupted in case of any of the following conditions apply: death; disease recurrence; diagnosis of second primary malignancy; referred to another center; unable to perform follow-up visits (e.g., due to comorbidities); the participant asked to exit the trial, but allowed the research team to keep patients’ data that they already have collected to be used for research analysis; the participant withdrew his/her consent to the whole study, and wants his/her data to be deleted forever for any future analysis; the participant withdrew his/her consent to the whole study, and wants his/her data to not be used for any future analysis.

Moreover, the participant will discontinue the study when a decrease ≥10 points of global health-related EORTC QLQ-C30 QoL [clinically meaningful deterioration, as defined in (13, 14)] is detected between two questionnaires completed 6 months apart. This will be considered an event for the primary endpoint.

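### Ending participation at the first 10-point global drop, or at recurrence, cuts short the domain-type secondary endpoints and removes follow-up that the survival-association and QALY analyses need

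*Protocol article*

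**What the plan says.** The exit rule appears twice in the protocol article. Section 2.2 states that when a clinically relevant global-health deterioration "is detected during the study period, the subject participation in the study will be interrupted"; its reason is that the patient's primary-endpoint status is then settled. Section 2.6.7 says "the participant will discontinue the study when a decrease ≥10 points of global health-related EORTC QLQ-C30 QoL" is found between two questionnaires six months apart. The same section lists other exits: "Participation in the study will be interrupted in case of any of the following conditions apply: death; disease recurrence; diagnosis of second primary malignancy", among others.

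Several planned analyses need data beyond that point:

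- Table 1 (section 2.1) has three secondary endpoints that are proportions deteriorating on other measures over up to 24 months: 3 QLQ-C30 scales, 8 QLQ-HN43 scales and 5 EQ-5D-5L domains, 16 in all.
- Table 2 plans "Association of disease-free survival (DFS), event-free survival (EFS) and overall survival (OS) with clinically relevant variations" in QoL, in one objective as time-dependent variations, and an incremental cost per QALY.
- Section 2.6.3 says that data on overall survival and "disease-free survival, DFS) will be collected up to 24 months from randomization".

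Section 2.6.3 does not say whether it applies after exit. Section 2.6.1 allows registry data for patients lost to follow-up, by consent and for Lombardy only.

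**The concern.** The rule suits the primary endpoint, because one event settles it. It does not suit endpoints for which the drop is only an intermediate event. A patient whose global health falls at month 6 gives no HN43, C30-domain or EQ-5D-5L data at months 12, 18 and 24, although those endpoints are defined over the whole period. Observation of the secondary endpoints therefore ends according to the primary outcome. If the platform lowers the drop rate, its patients stay under observation longer and have more opportunities to record a domain deterioration, so a successful platform is penalised on its own secondary endpoints.

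For the exploratory objectives, the patient leaves at the moment the exposure (a global drop) is recorded, so later recurrence or death is not seen. Death after recurrence is also unseen. The EQ-5D-5L course after the drop, which the QALY calculation needs, is missing. No analysis plan can recover questionnaires that were never sent.

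**Working it through.** **Inputs from the document.** Section 2.5.1: the proportion with a drop "in the control group is 20"%, and the proportion "during FU in the intervention group is 10"%; one-sided α 0.05; 80% power; 112 + 224 evaluable; 20% drop-out; 140 + 280 randomised. Section 2.2: follow-up questionnaires at months 6, 12, 18 and 24, so four per patient.

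**The plan's own figure.** A pooled one-sided two-proportion calculation at 2:1 gives 114 + 228; at 112 + 224 the power is 79.5%. Drop-out inflation: 112/0.8 = 140 and 224/0.8 = 280, total 420. The sample size is reproduced within rounding. It rests only on the proportion with a first drop, so the exit-at-drop rule does not affect it.

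**Assessments lost.** Assumptions: constant risk h per six-month visit, exit after the visit that shows the drop, no other drop-out.

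- h = 1 − (1 − p)^(1/4). Control, p = 0.20: h = 0.0543. Intervention, p = 0.10: h = 0.0260.
- Visits lost per patient = Σ h(1 − h)^(k−1)(4 − k), k = 1 to 4. Control 0.314; intervention 0.153.
- Share of the four visits: 0.314/4 = 7.8%; 0.153/4 = 3.8%.
- In numbers: 140 × 0.314 ≈ 44 of 560; 280 × 0.153 ≈ 43 of 1120.
- Gone before the month-24 assessment: 1 − (1 − h)^3 = 15.4% (about 22 of 140) versus 7.6% (about 21 of 280).
- If every drop came at month 6, the loss would be 0.20 × 3/4 = 15% versus 0.10 × 3/4 = 7.5%.

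**Effect on a domain-type endpoint.** The document gives no domain risks, so all of them below are assumptions.

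1. *No true effect on the domain.* With a 24-month domain rate of 20% to 40% and a within-visit correlation with the global drop of 0 to 0.5, simulation (1,000,000 per arm) shows the observed proportion 0.65 to 1.5 points lower in control than in intervention. Example: 30% in both arms, no correlation, is observed as 27.8% versus 29.0%.
2. *Domain risk rises with the global drop*, at the planned 20% versus 10%. Per-visit domain risk is 5% before and 15% after, or 10% and 25%. Differences are control minus intervention, in points:

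| When the higher risk starts | Risks | Difference with full follow-up | Difference observed |
|---|---|---|---|
| At the drop visit | 5% / 15% | +2.0 | +0.2 |
| At the drop visit | 10% / 25% | +2.4 | 0.0 |
| Only at the next visit | 5% / 15% | +1.3 | −0.7 |
| Only at the next visit | 10% / 25% | +1.6 | −1.3 |

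The shift is 1.8 to 2.9 points against the platform. Together with item 1, the bias at the planned rates is about 1 to 3 points.

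**Exploratory objectives.** Reading the sections side by side: on sections 2.2 and 2.6.7 a patient with a global drop has no follow-up after it, and a patient with recurrence has none towards later death. On section 2.6.3, survival and disease status run to month 24. These agree only if section 2.6.3 is meant to apply after exit, which the article does not say. Even then it covers disease outcome only, not QoL or EQ-5D-5L.

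**The case against.** The best defence has four parts.

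- **The interruption may be narrow.** It could mean only the end of app and questionnaire participation, with outcome data continuing under section 2.6.3 and routine clinical follow-up. The article also condenses a fuller protocol. This stands as far as survival is concerned: the text is ambiguous, and a definite loss of survival follow-up cannot be claimed. It does not rescue the questionnaires, for which no continuation is stated.
- **The bias is modest and conservative.** It runs against the platform, so it cannot by itself produce a false claim of benefit, and with equal drop rates both arms are truncated alike. This stands.
- **The main analyses are untouched.** The primary endpoint is settled at the drop, and time to first global deterioration has the drop as its own event. This stands for the drop rule; exit at recurrence still censors the time-to-event endpoint.
- **Part of the exploratory work survives.** Improvements, and deteriorations on scales other than global health, do not trigger exit. Recurrence is itself a DFS event. EQ-5D-5L is scheduled at the drop visit, so the fall itself is recorded. This stands.

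Two stronger readings are tempting. A reader might infer that the truncation reverses the sign of secondary effects. In the table above that happens only if domain risk stays low at the very visit that records the drop. All instruments are completed at the same visits, and if the higher risk applies there, the result is attenuation to about zero. A reader might also infer that the survival associations cannot be estimated at all; the last bullet shows why that is too broad.

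**Conclusion.** The point holds in limited form. The exit rule truncates the three domain-type secondary endpoints according to the primary outcome. At the protocol's 20% versus 10% and constant risk per visit, 7.8% versus 3.8% of follow-up assessments are lost. If the platform works, the domain comparisons are biased against it and much of a real secondary benefit can disappear. The size, about 1 to 3 points, rests on domain risks that the document does not give.

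For the exploratory objectives, three things lose their follow-up on the exit rules as written: the association of a global drop with later DFS, EFS and OS; OS after recurrence; and the EQ-5D-5L course after the drop. Section 2.6.3 conflicts with sections 2.2 and 2.6.7 unless it is meant to apply after exit.

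**What to change.** - Record the first drop of at least 10 points as the primary event without ending data collection.
- Continue the already scheduled web questionnaires, and disease and vital-status collection, to month 24 in both arms. Collect vital status after recurrence as well.
- Reconcile sections 2.2 and 2.6.7 with section 2.6.3, stating which data continue after each type of exit.

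Platform access and clinical management after the event are for the sponsor to decide and are not part of this change.

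Cost: a protocol amendment and about 1.6 further scheduled questionnaire rounds per patient with an event (0.314/0.20 = 1.57 in control; 0.153/0.10 = 1.53 in intervention). Section 2.6.5 already allows remote completion. The sample size stays at 420. At the planned rates, and ignoring other drop-out, the change recovers about 44 control and 43 intervention assessments.
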